### Blinding

Due to the obvious visible differences in treatment, it is not possible to blind the investigator or the participating patient.

### Statistical methods

For the primary outcome, the measure for non-inferiority of the success rate of the experimental group compared to the control group will be tested by a one-sided equivalence test for the success parameter of the underlying binomial distributions. The significance level for the one-sided equivalence test is 2.5%. All patients that are randomized and followed up for 24 months as well as all patients with an implant failure will be statistically analyzed. The secondary endpoints (improvement of the chewing efficiency and improvement of the oral health related quality of life after the intervention) will be addressed by non-parametric tests for non-inferiority of the experimental group compared to the control group. Non-inferiority of prosthetic complications will be analyzed by one-sided equivalence tests.

In the case of an implant failure in the experimental group, the patient will be treated according to the protocol of the control group with a new implant. Those patients will be excluded from the trial before retreatment. If more than 20% of the implants fail in any group within the first 3 months after implant placement, the study will be terminated. This criterion will be checked every 6 months after the inclusion of the first patient.

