## Background

Edentulism still occurs in elderly people in Germany and all over the world. In Germany, 30.5% of the population between 65 and 74 years are edentulous in the maxilla and/or mandible and 22.5% are completely edentulous [1]. Over the years there has been a strong consensus in dentistry that at least two implants are required to retain a complete denture in the edentulous mandible [2,3]. Indeed, two implants in the interforaminal area have high implant success rates and improve masticatory function [4-6]. In addition, a systematic review on the standard care for an edentulous mandible concluded that there is no strong evidence supporting a single standard of care for the edentulous mandible [7]. For elderly patients with a severely resorbed mandible, the use of implants is considered a medical necessity to retain dentures adequately and to reduce the resorption rate of the residual ridge in the anterior mandible. But as edentulism is often connected to having a low income [8], many patients cannot afford an implant therapy with two implants.

The concept of a single median implant in an edentulous mandible was introduced by Cordioli in 1993 [9] and the first 5-year results were published in 1997 with implant success rates of 100% [10]. A randomized clinical trial with 86 edentulous patients, compared mandibular overdentures retained by one or two implants [11]. Mandibular overdentures retained by a single median implant showed comparable satisfaction and maintenance time with lower component costs and treatment time than conventional two-implant overdentures during an observation time of 12 months. In these investigations, implants were left unloaded during healing. In 2010, Liddelow and Henry reported on a 100% implant-survival rate of immediately loaded implants after 36 months of observation when implants with oxidized surfaces were used [12]. Unfortunately, there was no control group with implants following a conventional healing protocol. However, Kronström *et al*. reported a failure rate of 17.6% after 12 months when immediate loading of a single median mandibular implant was applied [6]. So results of immediate loading of a single median mandibular implant retaining an overdenture are conflicting.

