### Sample size

The success rate of a single median implant after 2 years as the primary endpoint of the study is a binomial random variable and success probability is assumed to be 97% in the control group as well as in the experimental group. A maximum inferiority of 7% in the experimental group is regarded as clinically acceptable due to the benefits for these patients, i.e., avoiding the burden of a second procedure, having a stable denture directly after surgery and most probably reduced postoperative pain and discomfort, since the soft tissue of the surgical wound is not loaded with the denture during healing. Under these assumptions, a one-sided test of binomial parameters at a 2.5% significance level has a power of 80% to reveal the non-inferiority of the immediately loaded median implant if the sample size is 148 (74 per group). Taking into account a loss to follow-up rate of approximately 20%, a total of 180 patients (90 per group) was considered necessary [18]. It was assumed that the reasons for loss to follow-up would be random with respect to treatment assignment.

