## Discussion

This randomized clinical trial is designed to show the suitability of immediate loading of single median implants in an edentulous mandible. It is hypothesized that there will be non-inferiority of implant success for the experimental group compared to the control group.

Present clinical trials investigating a single midline implant in an edentulous mandible are mostly designed with a small number of patients [6,19,20]. Due to the sample size required for our clinical trial, a multi-center design is necessary. Taking into account a loss to follow-up rate of approximately 20%, a total of 180 patients (90 per group) was considered necessary. The loss to follow-up rate of 20% appears rather conservative but this rate also takes into account the exclusion of patients due to stopping criteria, e.g. compromised implant stability. In one study on immediate loading of a single mandibular implant, only 1 out of 17 implants (5.9%) did not achieve a minimum insertion torque of 30 Ncm [6]. In another study of immediate loading, only 2 out of 27 implants (7.4%) with oxidized surfaces did not achieve an insertion torque of 45 Ncm; however, the insertion torque actually obtained for these two implants was not reported [20]. From these studies, it is assumed that in our trial the number of patients excluded due to compromised implant stability and loss to follow-up will be less than 20%.

In a pilot study conducted at the University of Kiel, 11 patients were treated with one median implant in the mandible [21,22]. During this pilot trial, six implants followed a non-submerged healing protocol and were provided with a healing abutment and thus loaded moderately. No implant failed. The initial idea for the present clinical trial was to design a third treatment group as another experimental group with implants healing unsubmerged and moderately loaded over the healing abutment. However, for this three-arm study design, 354 patients would need to be allocated to the trial, as 282 patients would be needed for analysis. This number of patients would not have been feasible, especially in terms of finance. The idea of the present clinical trial is to compare two different healing protocols and not two different treatment options. The non-inferiority of one versus two implants in an edentulous mandible was shown by Walton *et al*. in 2009 [11]. A third treatment group with two implants in the interforaminal area was thus not considered necessary.

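### The stated 80% power at one-sided 2.5% with 74 per group is not delivered: exact power is about 70% with the unpooled test and about 54% with a score test that holds the level

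*Protocol article*

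**What the plan says.** The Sample size section gives all the planning inputs.

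- Success: "success probability is assumed to be 97% in the control group as well as in the experimental group".
- Margin: "A maximum inferiority of 7% in the experimental group is regarded as clinically acceptable".
- Level and power: "a one-sided test of binomial parameters at a 2.5% significance level has a power of 80"%, "if the sample size is 148 (74 per group").
- Recruitment: "Taking into account a loss to follow-up rate of approximately 20%, a total of 180 patients (90 per group) was considered necessary".

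The Statistical methods section repeats the level: "The significance level for the one-sided equivalence test is 2.5"%. It describes the primary test only as a one-sided equivalence test on binomial success parameters and names no statistic. The analysis takes randomised patients with 24 months of follow-up plus every patient whose implant failed.

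The Discussion gives a second planning figure, for a three-arm design that was not pursued: "354 patients would need to be allocated to the trial, as 282 patients would be needed for analysis". On delayed loading of a single median implant, the Background reports that "the first 5-year results were published in 1997 with implant success rates of 100"%.

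**The concern.** With 97% success and 74 per group, about 2.2 failures per group are expected (74 × 0.03). With so few events, large-sample tests on a risk difference can differ sharply in both power and true error. The stated level, size and power therefore need to belong to one test that holds its level.

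Two things are at stake. If the power is overstated, a loading protocol that really is equivalent has a much larger chance of ending inconclusive than the plan admits. If the higher power is sought through a test that exceeds its nominal level, the risk of accepting an inferior protocol is larger than 2.5%.

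**Working it through.** **Inputs** (Sample size section): success 0.97 in both groups, margin 0.07 read as absolute, one-sided level 2.5%, power 80%, 74 analysed per group, 90 randomised per group.

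**1. Reproducing the plan's figure.** Unpooled normal approximation:

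n per group = (z_level + z_power)² × 2 × 0.97 × 0.03 / 0.07²

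- One-sided 2.5%: (1.960 + 0.842)² × 0.0582 / 0.0049 = 93.2, so 94 per group (188 in total).
- One-sided 5%: (1.645 + 0.842)² × 0.0582 / 0.0049 = 73.4, so 74 per group (148 in total).

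The stated 148 appears only at 5%. The 2.5% result of 94 matches the three-arm figure in the Discussion, 282 = 3 × 94, if equal arms are assumed. Other formulas tried do not give 74 at either level: the score formula gives 136 (2.5%) and 105 (5%), arcsine 180 and 142, Fleiss 194 and 153.

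**2. Power at the stated level, by formula.** The standard error with 74 per group is √(0.0582/74) = 0.0280. Power = Φ(0.07/0.0280 − 1.960) = Φ(0.536) = 70.4%.

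**3. Exact power and exact error.** All outcomes of two independent binomials were enumerated at nominal one-sided 2.5%. Power is at 97%/97%. Error is on the null boundary, with experimental success 7 points below control. The 72 row is 90 less a full 20% loss.

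| Analysed per group | Test | Power | Error, control 97% | 98% | 99% | 100% |
|---|---|---|---|---|---|---|
| 72 | unpooled | 71.2% | 4.2% | 5.0% | 6.9% | 11.2% |
| 72 | score | 46.9% | 2.0% | 1.6% | 1.3% | 0.5% |
| 74 | unpooled | 70.2% | 3.8% | 4.5% | 6.2% | 10.2% |
| 74 | score | 53.7% | 2.2% | 2.1% | 1.7% | 0.5% |
| 90 | unpooled | 78.9% | 4.1% | 4.7% | 5.2% | 4.4% |
| 90 | score | 61.4% | 1.8% | 1.8% | 1.8% | 1.1% |

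With 90 per group the unpooled test's error peaks at about 5.3%, near 99.3% control success.

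**4. Why the tests differ.** Largest number of experimental failures that still gives non-inferiority, 74 per group:

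| Control failures | 0 | 1 | 2 | 3 |
|---|---|---|---|---|
| Unpooled | 2 | 2 | 2 | 3 |
| Score | 0 | 1 | 2 | 2 |

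Results of 0 versus 2, 1 versus 2 and 3 versus 3 (control versus experimental) pass one test and fail the other. The top-right error for 74 per group can be checked by hand. With no control failures, the unpooled test passes at up to 2 experimental failures. For 74 patients with failure probability 0.07, P(at most 2) = 0.0047 + 0.0259 + 0.0712 = 10.2%.

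**The case against.** A reader might infer that the plan prescribes the unpooled test and so fails to hold its own 2.5% level. The documents do not support that. Neither section names a statistic, and the wording fits a score or exact test equally well. A planning formula does not fix the analysis test, and the choice of statistic is commonly left to the full protocol or analysis plan, which are not shown. The sentence setting the level is not wrong in itself. The link to the unpooled formula is also indirect: it gives 148 only at a level the article never states, and the match to 282 needs equal arms and 2.5% per comparison, which the Discussion does not specify.

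Nor should 10.2% be read as the trial's error rate. It belongs to 74 per group and 100% control success; with 90 per group the value at 100% is 4.4%. The plan assumes 97%, whatever the Background reports for one earlier series. The 3.8% arises at 97% versus 90%, where about 7.4 experimental failures are expected (74 × 0.10), not at the planning alternative with about 2.

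All of this stands, and it makes the error-rate part conditional. It does not touch the power statement, which uses only the article's own inputs and fails with both tests examined.

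**Conclusion.** The Sample size section is wrong as written. At one-sided 2.5% with 74 analysed per group, power is about 70% (unpooled) or about 54% (score), not 80%. Even with all 90 per group analysed, exact power is about 79% and 61% respectively.

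The caution about the level is conditional. If the analysis used the unpooled test, the true one-sided error would be 3.8% at 97% versus 90% with 74 per group and 4.1% with 90. At 100% control success it would be 10.2% with 74 and 4.4% with 90. The score test stays at or below about 2.2% at the points tabulated. The higher power figure thus comes from the test that does not hold 2.5%.

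These results assume an absolute 7-point margin, equal groups and independent binomial outcomes. The power of an exact unconditional test was not calculated.

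**What to change.** - **Sample size:** restate the power at one-sided 2.5% for the test that will be used. For the score test at 97%/97% and a 7-point margin this is about 54% with 74 per group and about 61% if all 90 are analysed. Reconcile 148 with the stated level, since the unpooled formula gives it only at 5%.
- **Statistical methods:** replace the generic description of the primary test with a Farrington-Manning (Miettinen-Nurminen) score test and its confidence limit for the risk difference against -7 percentage points, or an exact unconditional test, at one-sided 2.5%. If the unshown full protocol already names such a test, cite it and give the power for it.

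The cost is one sentence and one corrected figure, with no extra patients or data. The drawback is that the stated power falls well below 80%.

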### Stopping criteria

A patient will be removed from the trial if any of the following occur:

– Any complication during implantation.

– A minimum insertion torque of 30 Ncm and/or a minimum implant stability quotient of 60 is not achieved (the patient will not be randomized and will be treated as the control group).

– An allergic reaction to titanium.

– A serious adverse event related to the implantation.

– Any relevant deterioration in the health of the subject possibly affecting participation in the trial.

– Failure to comply with trial requirements.

– Withdrawal of consent.

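### The primary analysis set is defined by the outcome: implant failures at any time are kept, failure-free early leavers are dropped, so the proportion does not estimate 24-month success

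*Protocol article*

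**What the plan says.** - **Statistical methods** sets the primary population: "All patients that are randomized and followed up for 24 months as well as all patients with an implant failure will be statistically analyzed". The test is a "one-sided equivalence test for the success parameter of the underlying binomial distributions", at a one-sided 2.5% level. The article describes no time-to-event or all-randomised primary analysis.
- **Sample size** defines the endpoint as the success rate after 2 years. It plans 74 analysed and 90 enrolled per group, allowing about 20% loss. On that loss it says: "It was assumed that the reasons for loss to follow-up would be random with respect to treatment assignment".
- **Stopping criteria** removes patients for several reasons, among them "A serious adverse event related to the implantation". For low primary stability it adds that "the patient will not be randomized and will be treated as the control group".
- **Discussion** says that the 20% also covers exclusions under the stopping criteria, such as compromised stability.
- **Outcomes** defines success by modified published criteria, which is wider than absence of implant failure. **Blinding** says that neither patient nor investigator can be blinded.

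**The concern.** The two halves of the rule treat incomplete follow-up differently. A failure seen before a patient leaves stays in numerator and denominator. A patient who leaves without failure is removed from the denominator, although that patient contributed failure-free time. The set is neither all randomised patients nor 24-month completers, and its success proportion does not estimate the 2-year success rate for which the trial was sized.

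The assumption about random loss does not repair this. If it holds, both arms' failure rates are still inflated, and a true difference is still stretched. If it fails, the difference moves with the drop-out pattern. That is possible here: the trial is unblinded, and only controls wait 3 months unloaded and have second-stage surgery.

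At stake is the single primary conclusion, judged against a 7-point margin with few expected failures.

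**Working it through.** **Inputs from the article.** Planning rate: "success probability is assumed to be 97% in the control group as well as in the experimental group". Margin: "A maximum inferiority of 7% in the experimental group is regarded as clinically acceptable". Level 2.5% one-sided; 74 analysed and 90 enrolled per group. The implied loss is 1 - 148/180 = 17.8%; the text says about 20%.

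**Assumptions, not in the article.** Drop-out is uniform over 24 months and independent of failure. Failure timing ranges from all in the first 3 months to evenly spread over 24. A middle case puts 70% in the first 3 months and the rest evenly over months 3-24.

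**The plan's own figure.** n per group = 2p(1-p)(z_α + z_β)²/δ², with 2 × 0.97 × 0.03 = 0.0582 and δ² = 0.0049.
- One-sided 2.5%: 0.0582 × (1.960 + 0.842)² / 0.0049 = 93.2, so 94.
- One-sided 5%: 0.0582 × (1.645 + 0.842)² / 0.0049 = 73.4, so 74.

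The stated 74 is thus not reproduced at 2.5%; at that level it gives 70.4% power. This is a separate matter, but it means that the power figures below, all at 2.5%, start below 80%.

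**Apparent failure rate.** With true failure f, drop-out d and s the share of failures seen before drop-out, the rule gives fs / (fs + (1-f)(1-d)).
- All failures seen (s = 1), d = 20%: 0.03 / (0.03 + 0.97 × 0.80) = 3.72%.
- All seen, d = 17.8%: 0.03 / (0.03 + 0.97 × 0.822) = 3.63%.
- Failures spread over 24 months (s = 1 - d/2 = 0.911), d = 17.8%: 0.02733 / (0.02733 + 0.79734) = 3.31%.

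**Difference at the margin (10% experimental, 3% control).** In the middle timing case the mean failure time is 0.7 × 1.5 + 0.3 × 13.5 = 5.1 months, so s = 1 - d × 5.1/24.

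| Drop-out, experimental / control | Apparent failure | Apparent difference (true 7.0) |
|---|---|---|
| 20% / 20% | 11.74% / 3.57% | 8.2 |
| 10% / 20% | 10.78% / 3.57% | 7.2 |
| 5% / 30% | 10.37% / 3.97% | 6.4 |

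For an extreme of 0% against 40% with all failures seen, the difference is 10.0 - 4.9 = 5.1 points, and the nominal 2.5% error becomes about 6.5%. With equal true failure of 3% and all failures seen, 30% against 10% drop-out gives 4.23% against 3.32%, a spurious 0.9 points.

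**Power at 97% in both arms.** For the stated set, power = Φ(δ / √(2p(1-p)/n) - 1.960), with p the apparent failure rate and n the number analysed. Example: p = 3.68%, n = 72.5 gives 0.07/0.0313 - 1.960 = 0.28, so 61.0%. Kaplan-Meier uses all randomised patients with the Greenwood variance.

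Part of the 20% is lost before randomisation. The Discussion cites 5.9% and 7.4% of implants below the torque thresholds of two earlier studies. Taking these off 90 per group leaves 84.7 or 83.3 randomised, so reaching 74 needs only 12.6% or 11.2% later drop-out.

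| Setting | Stated set | Kaplan-Meier | Gap (points) |
|---|---|---|---|
| 90/group, 20%, failures in first 3 months | 61.0% | 78.1% | 17 |
| 84.7/group, 12.6%, failures in first 3 months | 65.4% | 75.8% | 10 |
| 83.3/group, 11.2%, failures over 24 months | 68.0% | 72.9% | 5 |
| 90/group, 20%, middle timing, simulated, normal bound | 65% | 78% | 13 |
| Same, MOVER-Wilson bound | 46-47% | 60% | 13-14 |

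In the simulation the normal-approximation Kaplan-Meier bound rejects about 4% of the time at the margin, not 2.5%. The 78% is therefore optimistic, and a small-sample bound is needed.

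**The case against.** The strongest defence is that the effect is modest and mostly on the safe side. Inflation is about half a point. Equal drop-out widens the difference and so works against a false claim of non-inferiority; 10% against 20% still leaves it at 7.2. The 5% against 30% pattern has no support in the article, and even there the stated rule rejects about 4.1% of the time, against 4.3% for full follow-up with the same normal bound. Much of the power loss was planned when 148 was raised to 180: 74 analysed at 3% failure already gives 70.4%, and inflation takes it to about 66%. Kaplan-Meier itself needs censoring unrelated to failure. All this stands. It limits the severity and calls for ranges, but it does not make the proportion an estimate of 24-month success.

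A reader might infer more than the document supports:
- **That the power loss is a fixed 13 points.** That is one scenario; 5-17 is the defensible range.
- **That removals under the stopping criteria favour non-inferiority**, for instance that three removals in 90 hide 3.3 points. Such a count is hypothetical. Randomisation follows implant placement, both arms receive the implant, and only controls have second-stage surgery, so neither imbalance nor its direction is shown.
- **That failures in non-randomised, low-stability patients enter the control arm.** The failure clause does not repeat the word randomised, but those patients are removed from the trial and have no allocated arm. This is a wording point.
- **That every non-success is kept.** The clause keeps implant failures only. A leaver who had missed the success criteria in another way is dropped.

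Sensitivity analyses may sit in an analysis plan that is not shown, so their absence is no part of this point.

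**Conclusion.** The point holds as a should-fix. The article states a primary set whose membership depends on the outcome, and random loss with respect to assignment does not cure it. The shift is small in absolute failure at the planned rate, conservative at the margin when drop-out is equal, and anti-conservative only when controls leave much more often than experimental patients. The avoidable power loss is the more tangible cost. All sizes rest on the assumed drop-out pattern and failure timing, and on the stated 2.5% level.

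**What to change.** - Analyse all randomised patients in their allocated group.
- Estimate 24-month success with a method that handles censoring, for example Kaplan-Meier with patients without failure censored at their last visit. State the time origin, because follow-up runs from loading and controls are loaded 3 months later.
- Base non-inferiority on the 24-month difference with a one-sided 97.5% small-sample bound, such as MOVER-Wilson or log-log.
- Say that the failure clause applies to randomised patients only.
- Keep the present set as a sensitivity analysis. Because Kaplan-Meier also assumes censoring unrelated to failure, add one analysis that counts implant- or treatment-related removals as non-success, and a tipping-point analysis for withdrawals. Counting removals as non-success changes the endpoint, so it belongs among the sensitivity analyses and not in the primary analysis.

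The cost is revised wording, a little programming and a slightly more complex primary analysis. No new patients or data are needed.

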### Study sites

Prosthetic departments of dental schools in Germany interested in clinical research were informed of the design and the aims of this study. Nine departments decided to participate. Each department designated an investigator responsible for patient examinations and follow-up visits and a clinician responsible for patient treatment (implant placement and second-stage surgery).

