### Intervention

Two treatment groups are defined. For the experimental group, the median implant is immediately loaded after placement using a ball attachment and a matrix, which is integrated into the existing denture base intraorally. For the control group, the median implant is left unloaded and allowed to heal submerged for 3 months. The implant is loaded after second-stage surgery using a ball attachment and an intraorally placed matrix.

To avoid bias, randomization is conducted after implant placement and primary implant stability measurement by opening a sealed envelope. Neither the patient nor the study team knows the treatment group at the time of implant placement. Randomization is performed centrally by the trial statistician using block randomization with variable block size and an allocation ratio of 1:1. Stratification is according to the patient’s residual bone height (Class II or III according to McGarry *et al*. [14]) and the study center.

All interventions are conducted according to defined standard operating procedures. During the first calibration meeting, videos demonstrating the clinical und surgical procedures are shown. These are made available to all participating study centers. The first implant placement in each center is supervised by the treatment coordinator of the leading center. Experienced clinicians perform the surgical and prosthetic procedures.

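### The chewing and quality-of-life endpoints are planned as tests of improvement scores with no baseline or stratification term named; adjusting the follow-up score would be more precise at no data cost

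*Protocol article*

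**What the plan says.** All references are to the protocol article.

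- **Intervention:** allocation uses "block randomization with variable block size and an allocation ratio of 1:1". On the factors it says "Stratification is according to the patient’s residual bone height", with two McGarry classes (II and III), and it adds study center.
- **Study sites:** "Nine departments decided to participate", so the two factors form 2 × 9 = 18 strata.
- **Statistical methods, secondary endpoints:** these are "improvement of the chewing efficiency and improvement of the oral health related quality of life after the intervention". They are to be examined with non-parametric tests of non-inferiority. No baseline covariate, stratum or center term is named.
- **Statistical methods, primary endpoint:** a "one-sided equivalence test for the success parameter of the underlying binomial distributions", again with no strata named.
- **Methods/design:** the article states that a detailed study protocol exists. It is not at hand.

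A baseline measurement of chewing function and quality of life is implied by the word improvement. The Outcomes section lists only the visits after loading or placement, and the trial chart (Figure 1) is not shown.

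**The concern.** The form of the secondary endpoints (improvement) and the family of tests (non-parametric) are stated choices. An improvement score fixes the weight given to baseline at exactly 1. When the correlation between baseline and follow-up is moderate, that weight is too large, and noise in the baseline score is carried into the comparison. A regression on baseline estimates the weight instead. Bone-height class and center, if they predict the scores, would remove further variance.

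These endpoints matter to the trial. The Background makes earlier improvement in quality of life and chewing function a stated aim. They are tested for non-inferiority, so an interval wider than it need be raises the chance of an inconclusive result. The Discussion says that a larger three-arm design was not feasible, mainly for financial reasons. Precision from measurements already taken is therefore worth having.

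**Working it through.** **1. Is there a figure in the plan to reproduce?** Not for the secondary endpoints: the article gives no SD, correlation, margin or sample size for them. The check below therefore rests on a formula and an assumed range.

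**2. Variance of the two analyses.** Let the follow-up SD be s1, the baseline SD s0 and their correlation r. Per patient and for means:

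- improvement score: s1² + s0² − 2·r·s0·s1
- follow-up adjusted for baseline: s1²·(1 − r²)
- difference: (s0 − r·s1)², which is never negative

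In large samples the adjusted analysis is therefore no less precise, whatever the SDs. The two are equal only when the regression slope r·s1/s0 is 1. With s0 = s1 the ratio is (1 − r²) / [2(1 − r)] = (1 + r)/2.

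**3. Numbers.** The range r = 0.3 to 0.8 is an assumption. The 74 analysed per group comes from the Sample size section.

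| r | Variance ratio (1+r)/2 | Extra patients for the same precision, 1/ratio − 1 | Patients per group on improvement scores that match 74 adjusted, 74/ratio |
|---|---|---|---|
| 0.3 | 0.65 | 54% | 114 |
| 0.5 | 0.75 | 33% | 99 |
| 0.6 | 0.80 | 25% | 92.5 |
| 0.7 | 0.85 | 18% | 87 |
| 0.8 | 0.90 | 11% | 82 |

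Confidence intervals shrink by the square root of the ratio: √0.65 = 0.81 and √0.90 = 0.95, so they are about 5 to 19% narrower. Any gain from bone-height class and center is not counted.

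**4. Can the model carry the extra terms?** Intercept, treatment, baseline, one class term and eight center terms make 12 parameters. With 148 patients, 148 − 12 = 136 residual degrees of freedom remain, which is ample for a continuous score.

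**5. Does the same argument apply to the primary endpoint?** The Sample size section states that "success probability is assumed to be 97% in the control group as well as in the experimental group".

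- Expected failures: 148 × 0.03 = 4.4. Over 18 strata that is about 0.25 per stratum of about 8 patients, too sparse for full stratification.
- Stratifying by bone-height class only, assuming two equal strata averaging 3% failure: the pooled variance is 0.03 × 0.97 = 0.0291. If failure risks are 2% and 4%, the average within-stratum variance is (0.0196 + 0.0384)/2 = 0.0290, a ratio of 0.997. With a tenfold risk ratio (0.55% and 5.45%) the ratio is 0.979.
- Power at 74 per group and one-sided 2.5%, by the normal approximation with the 7-point margin, moves from 70.4% to between 70.6% and 71.3%.

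**6. The separate power shortfall.** The unpooled formula n = (1.96 + 0.84)² × 2 × 0.97 × 0.03 / 0.07² gives 93.2, so 94 per group rather than 74. Stratification lowers 93.2 only to between 92.9 and 91.3. That discrepancy is a different matter and stratification does not close it.

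**The case against.** The strongest case against is that the article is silent on adjustment and does not reject it. Covariates and strata are commonly left to a full protocol or SAP, and a detailed protocol is said to exist. Rank ANCOVA is itself non-parametric, so the requested analysis may even fit the stated wording. A test of improvement in a randomized trial is unbiased, so no error is shown. The correlation is assumed, and the formula is a result for means with equal SDs, applied here to rank tests of unspecified form.

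Most of this stands and limits the point. A reader might infer that the plan prescribes unadjusted and unstratified analyses. The article does not say so: it names tests and leaves the rest open. What remains is that the endpoint is fixed as improvement, a stated choice that uses baseline less well than adjustment does. The choice of r changes the size of the gain but, for means in large samples, not its direction (step 2 of the working).

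A reader might also infer that the primary analysis gives away useful precision, or that stratifying it would restore the stated 80% power. Neither is supported. The gain is about 0 to 2% of variance, and a pooled test after stratified randomization stays valid and is at most slightly conservative.

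**Conclusion.** The point holds as an efficiency improvement for the two secondary scores, not as an error or a contradiction. Taken as written, the improvement-score analysis is less precise than a baseline-adjusted one by a variance ratio of about 0.65 to 0.90. This rests on an assumed correlation of 0.3 to 0.8, equal SDs at baseline and follow-up, and the use of a result for means as a guide to rank tests. It also assumes that both scores are measured at baseline, as improvement implies. For the primary endpoint the gain is negligible. The full protocol or an SAP may already specify the adjustment, in which case nothing needs changing.

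**What to change.** For chewing efficiency and oral health related quality of life, state that the follow-up score is compared between groups with adjustment for baseline score, bone-height class and center. Use ANCOVA with a robust or bootstrap confidence interval, set against the non-inferiority margin. If a non-parametric main analysis is preferred, use a rank-based equivalent such as rank ANCOVA. Keep the non-parametric test of improvement as a sensitivity analysis.

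For means, randomization makes the expected treatment difference the same for the adjusted follow-up score and for the improvement score. A margin set as a mean difference in improvement therefore carries over.

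For the primary endpoint, a risk difference stratified by bone-height class (Miettinen-Nurminen with Mantel-Haenszel weights) is optional. Center should stay out of that stratification, as 180/18 gives about 10 randomized patients per stratum. The gap between 74 and 94 per group needs its own correction.

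The cost is a few lines of SAP wording, settled before the data are analysed. No new visit, measurement or patient is needed.
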